#### Second phase: simulation-based training

The training at the next center starts at the end of the training of the previous center (duration per center: approximately 2 months).

The simulation-based training program is based on the pedagogical strategies described in simulation and seems to be relevant in this context, i.e., deliberate practice, mastery learning, and rapid cycle deliberate practice.

Peyton’s “4 steps” method is used for new learning. We will propose a variation of this learning tool that is more adapted for a group.

A “minimum passing score” (MPS) will be established on the main steps necessary to perform the procedure, including respect for good hygiene practices and effective communication. If the MPS is not reached, the learner can repeat the different workshops until an acceptable score is obtained (90% of correct answers).

The training will take place on a procedural mannequin, that is, an arm with a pulsatile AVF that is echogenic.

The training also includes a scenario with simulated patients using the “rapid cycle deliberate practice” method [19]. It is relevant to work on communication with the patient during procedural simulation.

#### Simulation-based training program

The program is composed of one-day training sessions at the NorSimS simulation center, with a maximum of 4 to 6 nurses per session. It includes different modules:Module 1/AVF puncture: theoretical review, puncture on simulator with application (location, examination, puncture, needle fixation, compression post puncture)Module 2/therapeutic communication: with simulated patientModule 3/ultrasound: manipulation with echogenic patches and AVF arms, ultrasound identification/guidanceModule 4/training restitution: This hybrid simulation consists of using a simulator for invasive procedures and a simulated patient for communication training

### Criteria for discontinuing or modifying allocated interventions {11b}

According to the French Law n° 2009–879 of July 21, 2009, on hospital reform, patients, health, and the territory, all health professionals are obliged to be trained. Thus, it has been agreed with the volunteer centers participating in this study that all nurses working in these services will participate in the training. However, patients can withdraw from the study at any time.

### Strategies to improve adherence to interventions {11c}

To ensure the motivation of the nurses in the control group, they will receive simulation-based training once all the data needed for the study have been collected.

Additionally, nurses are thanked for their participation in the whole study with a culture voucher of a total value of 100 euros. These vouchers will be distributed to the nurses who complete the entire study (pretraining, training, and posttraining survey).

### Relevant concomitant care permitted or prohibited during the trial {11d}

There is no prohibited concomitant care.

### Provisions for post-trial care {30}

There will be no provisions after this trial.

Due to interventional research type (low risk one), the sponsor took out an insurance policy specific for this study that will compensate if there is any injury attributed to the randomized control trial.

### Outcomes {12}

The primary outcome is the number of adverse events occurring during AVF puncture in the TT and TTST groups (comparison of percent occurrence of events in each group) defined by any of the following events: unipuncture failure, bipuncture failure, simple hematoma, hematoma not allowing continuation of dialysis.

The secondary outcomes are the number of perdialytic bleeds: accidental needle withdrawal, pain score (numerical scale) experience at the time of puncture, ease or difficulty of puncture, patients’ anxiety score (numerical scale) at the time of puncture, use of ultrasound by the nurse, and type of equipment used for the puncture (needle or catheter).

### Participant timeline {13}

The participant timeline is presented in Fig. 2

**Fig. 2 Fig2:**
[figure not shown]
Participant timeline

### Sample size {14}

This is a comparative, prospective, multicenter evaluation study taking place in 8 centers. The population is made up of all nurses performing hemodialysis punctures. We expect a reduction of at least 50% of the complications related to the puncture in the experimental group compared to the control group (possible result following the first pilot feasibility study, monocentric, prospective, observational, before/after, SIMFAV (RCT03680209) carried out at the University Hospital of Caen Normandy). To show a significant difference at T8, a minimum of 1 complication per day (the least favorable condition for confirming our hypothesis) was considered, i.e., over 4 weeks and for 8 centers, 224 complications in the control group, or 9.3%. For a reduction of at least 50% (4.65%), a risk *α* equal to 5%, and a power of 90%, it is necessary to have a total of 610 punctures, i.e., approximately 80 per institution. The randomization of hospitals and not of caregivers (registered nurse) allows us to avoid the risk of contamination between the two groups and to simplify the organization of the study within each institution. The Hawthorne effect should be reduced by the fact that, at the end of the study, the TT group will benefit in the same way as the TTST group from the procedural and hybrid simulation training. This should ensure that all the caregivers will adhere to the project and thus be motivated to do so in a perfectly equitable manner. The methodology of randomizing hospitals and not caregivers, the so-called cluster approach, leads to caregivers in the same cluster being more similar (intraclass/intracluster correlation, ICC) than caregivers from different institutions randomized globally. To correct for this impact on variance, it is necessary to apply a variance inflation correction factor equal to (1 + (*m*-1) *r*) to the required number of subjects, with *m* equal to the realized number of punctures within a cluster and *r* being the ICC. The value of *r* can be relatively high because of the way in which a facility or department performs its nursing practice. To be able to carry out all the analyses and to take into account additional analyses (center effect, effect of the number of punctures performed and the degree of experience of the nurse, etc.), and feasibility, the highest number of 600 punctures per center, i.e., 4800 punctures, 2400 per group, is used. This number of 600 punctures per center takes into account the number of establishments.

The same number of 4800 punctures for the T5 period (baseline) is also used. This means a total of 9600 punctures over the study period.

Several levels are taken into consideration: center, nurse, patient, and AVF puncture. Within a single center, the overall reflection of activity is related to history, practices, schedules, recommendations, etc. This center-specific activity may differ from one center to another. The experience of the nurses led to the same effects from one center to another, such as the characteristics of the patients and the AVF. These different points are taken into consideration to look for possible differences and effects that could be the cause of confounding factors.

In total, 8 centers participated, with 600 pretraining punctures per center and 600 posttraining punctures per center; that is, 9600 punctures were observed.

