## Statistical methods

### Statistical methods for primary and secondary outcomes {20a}

The difference in percentages between the two groups will be determined by a chi-square test, thus allowing us to meet the main objective. This result will be adjusted according to several criteria, two of them in particular: a center effect, a baseline effect, and an effect of the degree of experience of nurses.

Indeed, the analysis of cluster trials is more complex than the analysis of trials with individual randomization units. The analysis will therefore also be carried out at the cluster level using the guide of the French Health Authority of June 2007 (methodological guide downloadable from www.has-sante.fr).

The secondary objectives (number of per-dialytic bleeds, accidental needle withdrawals) will be analyzed according to the same procedures as for the primary objective. The pain score (numeric scale) at the time of puncture will be analyzed between the two groups by Student’s *t* test.

All the parameters collected will be analyzed.

Multivariate analyses will be considered according to the results of univariate analyses such as logistic regression comparing the two groups and mixed models.

The adjustments described above will also be applied to the secondary objectives.

The collection of the nurses’ feelings of expertise will be synthesized.

All analyses will be based on a first species error of 5% and will be two-tailed.

The IBM®-SPSS® data analysis software (IBM Corp. Released 2015. IBM SPSS Statistics for Windows, Version 23.0. Armonk, NY: IBM Corp.) will support all analyses.

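### The stated total of 610 punctures for 90% power does not reproduce: the plan's own inputs need about that many per group, roughly twice the total

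*Protocol article*

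**What the plan says.** The Sample size section {14} of the protocol article counts at least one complication per day, over 4 weeks and 8 centres, and arrives at "224 complications in the control group, or 9.3" percent. It halves this to 4.65% for the experimental group, takes a 5% risk and 90% power, and concludes that "it is necessary to have a total of 610 punctures, i.e., approximately 80 per institution".

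The section then turns to clustering: "To correct for this impact on variance, it is necessary to apply a variance inflation correction factor equal to" 1 + (m − 1)r, where m is the number of punctures in a cluster and r the intracluster correlation. It says that r may be fairly high, but gives no value and no inflated number. It adopts 600 punctures per centre, citing additional analyses, feasibility and the number of establishments: "4800 punctures, 2400 per group, is used".

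The Statistical methods section {20a} fixes the test and its sidedness: "The difference in percentages between the two groups will be determined by a chi-square test", and "All analyses will be based on a first species error of 5% and will be two-tailed".

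**The concern.** The wording calls 610 a total, and the division by institutions confirms that reading: 610/8 = 76, rounded to 80. Halving a rate of about 9% with 90% power would normally take more than 305 observations per group. If 610 is really a per-group number, the section states a size and a power that do not belong together.

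What is at stake is the starting point of the cluster calculation. The section says the inflation factor must be applied to the required number, and 610 is the only required number it gives. Anyone who judges 4800 against 610 would credit the design with about twice the tolerance for clustering that it has at the stated rates.

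**Working it through.** **Inputs.** p₁ = 0.093, p₂ = 0.0465, power 90%, equal groups (2400 each), from Sample size {14}. Two-sided 5% and chi-square test, from Statistical methods {20a}. So z(0.975) = 1.960 and z(0.90) = 1.282.

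**Step 1: try to reproduce 610 as a total.**

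Pooled chi-square formula: n per group = [1.960·√(2p̄(1−p̄)) + 1.282·√(p₁(1−p₁)+p₂(1−p₂))]² / (p₁−p₂)².

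- p̄ = 0.06975, so √(2p̄(1−p̄)) = 0.3602.
- √(p₁(1−p₁)+p₂(1−p₂)) = 0.3587.
- n = (0.7060 + 0.4597)² / 0.0465² = 628.5, so 629 per group and 1258 in total (1258/8 = 157 per centre).

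Arcsine formula: h = 2·asin√p₁ − 2·asin√p₂ = 0.1851, and n = 2(1.960 + 1.282)²/h² = 613.4, so 614 per group and 1228 in total (about 154 per centre).

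Other settings at the same rates:

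| Setting | Per group | Total |
|---|---|---|
| Two-sided, 90%, unpooled | 626 | 1252 |
| Two-sided, 90%, continuity-corrected | 671 | 1342 |
| One-sided, 90% | 500 to 555 | 1000 to 1110 |
| Two-sided, 80% | 459 to 512 | 918 to 1024 |
| One-sided, 80% | 361 to 412 | 722 to 824 |

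None gives 610 in total. As a per-group number, 610 is within 1% of the arcsine value and about 3% below the pooled one. With the unrounded rates 224/2400 and 112/2400, the arcsine formula gives 611.0 before rounding up. No formula returns exactly 610.

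**Step 2: power at the stated size.** Power = Φ{[(p₁−p₂)√n − 1.960·0.3602] / 0.3587}.

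| Punctures per group | Power under independence |
|---|---|
| 305 (610 in total) | 61.6% (62.9% by exact enumeration of the chi-square test) |
| 320 (80 × 8 = 640 in total) | 63.7% |
| 610 | 89.1% (89.7% by exact enumeration) |
| 2400 (adopted) | over 99.9% |

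**Step 3: effect on the clustering allowance.** The largest design effect that 4800 can absorb at 90% power is 4800 divided by the total required under independence:

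- base 610: 4800/610 = 7.9;
- base 1258: 4800/1258 = 3.8.

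With m = 600, the tolerable r is (7.87 − 1)/599 = 0.011 in the first case and (3.82 − 1)/599 = 0.005 in the second. The document gives no r, so the following values are assumptions. Power at 2400 per group, using 2400/(1 + 599r) as the effective size, is about 89% at r = 0.005, 67% at 0.01, 42% at 0.02 and 20% at 0.05. This is a normal approximation that ignores pairing, baseline adjustment and the small number of clusters.

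The base can decide the answer. At an assumed r = 0.01 the factor is 1 + 599 × 0.01 = 6.99. Then 610 × 6.99 = 4264, which is below 4800, but 1258 × 6.99 = 8793, which is well above it.

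**Step 4: the control rate.** 8 centres × 28 days × 1 per day = 224, and 224/2400 = 9.33%. The 2400 is the control group's allotment, which comes from 4 centres. One complication per day in each of 4 centres gives 4 × 28 = 112, and 112/2400 = 4.67%. Halving that to 2.33%, the pooled formula gives (0.5094 + 0.3324)²/0.02333² = 1301.6, so 1302 per group and 2604 in total.

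**The case against.** The strongest reply is that 610 is not the size of this trial. The section goes on to adopt 4800 punctures, almost four times 1258. Under the same independence assumption that yields 62%, the adopted size gives over 99.9% power. This stands. A reader might infer that the trial has been sized at 62% power, or that 4800 is inadequate because of this slip. The document supports neither.

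A second reply is that the section never multiplies 610 by a design effect and never claims an eightfold margin; it justifies 600 per centre on other grounds. This also stands. The 7.9 and 3.8 are what follows if the section's own correction is carried out, not figures that the authors printed. They also leave out the pairing of centres and the planned baseline adjustment. The absence of any value for r is a separate weakness that would remain after this correction.

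Third, it is tempting to say outright that 610 is the per-group number. That is a strong inference, not a proven fact, because no formula tried returns 610 exactly. What is shown is that 610 in total does not reproduce.

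None of this rescues the statement itself. It appears in running text, and the division by 8 institutions rules out a per-group reading of the sentence.

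**Conclusion.** The point holds as an error in the stated requirement. At 9.3% versus 4.65%, two-sided 5% and 90% power, the total under independence is about 1228 to 1258, not 610. A total of 610 gives about 62% power, some 28 points below the stated 90%. These results assume independent punctures, equal groups and the plan's own rates.

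The consequence is limited to the justification. The base figure for the cluster correction is about half of what it should be, so the design effect that 4800 can absorb at the stated rates is about 3.8 instead of 7.9. Whether 4800 is enough cannot be settled from the document, because r is not given. The corrected base is itself provisional: if the control rate is 4.67%, it roughly doubles again, to 2604.

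**What to change.** 1. Reconcile the control rate first. State whether the 224 complications belong to 8 centres or to the 4 control centres, and use a matching number of punctures as denominator.
2. Restate the requirement per group and in total under independence, and name the formula. With the pooled chi-square formula this is 629 per group and 1258 in total if 9.3% is kept, or about 1302 per group and 2604 in total if the rate is 4.67% halved. If the arcsine formula was used, say so and label its result (614 at 9.3%) as per group.
3. Replace the figure of about 80 per institution accordingly (about 157 for a total of 1258).
4. Apply the design effect to that base, stating the value or range of r assumed.

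This is a correction to the text. Planned enrolment and conduct need not change, but the stated power justification becomes less favourable.

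### The cluster inflation factor is called necessary but never applied, so the only stated power (90%) assumes independence; with 4 centers of 600 punctures per arm it holds only at a very small ICC

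*Protocol article*

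**What the plan says.** In the protocol article, Sample size {14} takes a control complication rate of 9.3% and expects it to be halved to 4.65%. With a type I error "equal to 5%, and a power of 90%, it is necessary to have a total of 610 punctures", it arrives at roughly 80 punctures per institution. No clustering enters this step.

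The section then explains that randomizing hospitals makes results within a hospital alike, and states that "it is necessary to apply a variance inflation correction factor equal to" 1 + (m − 1)r, where m is the number of punctures in a cluster and r is the ICC. It adds that r "can be relatively high because of the way in which a facility or department performs its nursing practice".

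No value of r, no computed factor and no inflated number follows. The section turns to the range of planned analyses, the additional analyses and feasibility, and concludes that "the highest number of 600 punctures per center, i.e., 4800 punctures, 2400 per group, is used". It adds that this figure allows for the number of establishments. No power is attached to the 4800.

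Implementation {16c} gives 4 centers in each group. Statistical methods {20a} states: "All analyses will be based on a first species error of 5% and will be two-tailed".

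**The concern.** The section identifies the right correction, says it must be made, and stops. The only power figure in the article therefore belongs to a calculation that the same paragraph calls incomplete.

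This matters because m is large and the number of clusters is small. At m = 600 the factor is 1 + 599r, so a small r inflates the variance several times over. With 4 centers per arm, extra punctures per center soon add little information about the training effect. A reader who carries the 90% over to the final design could take a null result as evidence against simulation training, although the chance of detecting a halving of events may have been far below 90%.

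**Working it through.** **Inputs.** Rates 9.3% and 4.65%, 5% type I error, 90% power, m = 600 and 2400 per arm are from Sample size {14}. The two-sided test is from {20a}, and 4 centers per arm from {16c}. The article gives no ICC, so every ICC below is an assumption, shown as a range. The 9.3% is taken as it stands.

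**Step 1: the plan's 610.** The pooled two-proportion formula is

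n per arm = [1.960·√(2p̄q̄) + 1.282·√(p₁q₁ + p₂q₂)]² / (p₁ − p₂)²

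with p̄ = 0.06975, 2p̄q̄ = 0.12977, p₁q₁ + p₂q₂ = 0.12869 and p₁ − p₂ = 0.0465. It gives 628.5, so 629 per arm and 1258 in total. Variants per arm are 626 (unpooled), 614 (arcsine), 671 (continuity-corrected) and 513 (one-sided). None gives 610 in total. Taken as a total, 610 is 305 per arm and about 62% power. It lies close to the arcsine number per arm, so it may be a per-arm figure labelled as a total; that is an inference.

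**Step 2: the largest tolerable ICC.** Effective n per arm = 2400 / (1 + 599r).

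- Normal reference: the factor may be at most 2400 / 628.5 = 3.82, so r ≤ 2.82 / 599 = 0.0047.
- t on 6 df (8 centers, 2 arms), solved numerically: r ≤ 0.0027.
- The plan's 610 taken at face value: 4800 / 610 = 7.87, so r ≤ 6.87 / 599 = 0.0115.

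**Step 3: power of 4 × 600 per arm, no baseline adjustment.** SE = √(0.12869 / effective n). For r = 0.01 the factor is 6.99, effective n is 343, SE is 0.01936 and 0.0465 / SE = 2.40. The normal power is Φ(2.40 − 1.96) = 67%; the noncentral t on 6 df gives 52%.

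| Assumed ICC | Factor | Effective n per arm | Power, normal | Power, t 6 df |
|---|---|---|---|---|
| 0.001 | 1.60 | 1501 | 99.9% | 98% |
| 0.005 | 4.00 | 601 | 89% | 75% |
| 0.01 | 6.99 | 343 | 67% | 52% |
| 0.02 | 12.98 | 185 | 42% | 32% |
| 0.05 | 30.95 | 78 | 21% | 16% |

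**Step 4: unlimited punctures.** As m grows, effective n per arm tends to 4 / r. At r = 0.01 this is 400, SE is 0.01794 and the ratio is 2.59. Power then cannot exceed about 74% (normal) or 58% (6 df).

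**Step 5: a possible gain from the baseline period.** The variance of a center's observed rate is proportional to r + (1 − r)/600. If the true center rates in the two periods correlate at ρ, the observed rates correlate at R = ρr / [r + (1 − r)/600], and adjustment multiplies the variance by 1 − R². At r = 0.01 and an assumed ρ = 0.8, R = 0.008 / 0.01165 = 0.687 and 1 − R² = 0.528. On 5 df, power is about 75% at ICC 0.01 and 56% at 0.02. With ρ = 0.5 it is 57% and 36%. A more generous version (normal reference, baseline sampling error ignored, ρ = 0.8) gives about 95%, 78% and 45% at ICC 0.01, 0.02 and 0.05.

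**The case against.** Four points can be made for the plan.

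- **The 90% is not claimed for the final design.** This stands. A reader might infer that the protocol promises 90% power for 4800 punctures, or that it says 600 per center covers clustering. It says neither: the 90% is attached to 610, and the 4800 carries no power at all. The defect is that the design has no cluster-adjusted power, so the unclustered figure is the only one a reader can use.
- **4800 is almost eight times 610, which is a generous allowance.** On the plan's own figure that covers an ICC up to 0.0115. But it needs 610 to be a correct total, and Step 1 shows it is not. Even 0.0115 fits poorly with a quantity that the section expects might be high.
- **The design has 4800 baseline punctures, planned baseline adjustment and matched pairs.** These may recover real power, as Step 5 shows, but the amount depends on a correlation that the article does not give, and Sample size {14} counts no such gain. Pairing can also cost power: analyzed as pairs on 3 df with no gain from matching, power at ICC 0.01 is about 38%.
- **The article condenses a fuller protocol.** An ICC may be given there. But this section itself starts the correction, calls it necessary and then fixes a size without it, so the gap lies in the published reasoning.

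The wording on the ICC is also only that it can be relatively high. That is a possibility, and the article does not assert that the ICC is high in these centers.

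**Conclusion.** The concern holds in this form: the correction that the plan calls necessary is not applied, and the adopted design reaches 90% power only at a very small ICC. Without baseline adjustment, the limit is about 0.0047 (normal) or 0.0027 (6 df). At assumed ICCs of 0.01 to 0.05, power runs from 67% down to 21% (normal) or from 52% down to 16% (6 df). These figures rest on the plan's own rates, equal centers of 600 and a two-sided 5% test.

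A reader might conclude that the trial is underpowered. The document does not establish that: the ICC is unknown, and at 0.001 power is about 98% or more even unadjusted. What it does show is that the power of this design is unstated and very sensitive to the ICC, and that more punctures per center cannot remove that sensitivity.

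**What to change.** In Sample size {14}:

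1. Say that the 90% applies only if punctures are independent, and correct or explain the total of 610.
2. Replace it, as the design's power, with power for 4 centers per arm and m = 600 over a stated ICC range (for example 0.001 to 0.05), with and without baseline adjustment. Name the reference distribution and the assumed correlation between periods.
3. State the largest ICC at which 90% holds.

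If the ICC is estimated from the baseline punctures, report it with its interval and do not treat it as settling the matter. With 8 centers of 600, an estimate of 0.01 would have an approximate 95% interval of 0.003 to 0.045 (ANOVA F method, approximate for a binary outcome).

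The cost is a paragraph and one table. No centers or punctures are added. The downside is a stated power less favorable than 90% over much of a plausible range.
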